### Outcomes

Primary endpoints include established measures of VR intervention feasibility^63^: acceptability will be measured with the System Usability Scale (SUS)^64^; tolerability will be measured with the Simulation Sickness Questionnaire (SSQ)^64 65^; intervention adherence is measured in minutes of completed VR exposure. We will administer all assessments on a per-session basis and use the means across sessions as dependent variables. Acceptable levels of feasibility (ie, the trial progression criteria) for the primary endpoints are defined as follows: (1) normative data for the SUS suggest that average scores below 50 indicate insufficient acceptability, and scores above 70 indicate sufficient acceptability^66^; (2) empirical evidence shows that 60–95% of participants experience some level of cyber sickness during VR exposure, as determined by an SSQ Score greater than 40.^67 68^ Given its high prevalence, we deemed that cyber sickness rates (ie, proportion of patients with an average, across-session SSQ scores≥40) exceeding 95% would clearly indicate the RCT as infeasible, whereas any rates below 60% would suggest the RCT is feasible; (3) adherence, according to our pilot data, refers to completing at least 12 min of exposure, at which point habituation onset can be observed. We reasoned that adherence rates should not be lower than 50% (ie, no fewer than half of the patients should complete the minimum amount of average exposure) and that it should ideally approach the average level estimated across other VR exposure therapies (84%^69^).

Secondary endpoints include (1) outcomes relevant to the mechanism of the intervention (ie, activity urges) and (2) clinical outcomes (to be evaluated in the full-scale RCT) as targeted by AN treatment guidelines.^21^ Activity urges will be recorded on a per-session basis using the validated state activity urges questionnaire (State Urge to be Physically Active-Questionnaire (SUPA-Q)).^55^ The clinical outcomes, monitored on a weekly basis, include changes in eating disorder psychopathology using the Eating Disorder Examination-Questionnaire (EDE-Q),^70^ as well as weekly weight gain, defined by changes in patient BMI (in kg/m²), which will be obtained from patient records.

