Safety and additional assessments include the rate of weight gain and potential moderators of intervention effects. Weight restoration is one of the primary goals in AN treatment.^10^ Current treatment guidelines propose weight gains of 500 g per week,^21^ though this is rarely achieved in a steady manner unless in tightly controlled settings.^24^ We reasoned the intervention would be unsafe, if successful weight gain rates in the intervention condition fall below the weight gain rates in the control condition. Potential moderators of intervention effects, to be evaluated in the full-scale RCT, include the Commitment to Exercise Scale (CES),^71^ and excessive PA status in the 28 days prior to admission, which we will assess at trial start during a face-to-face interview and categorise using the criteria: (1) ≥1 hour a day and ≥5 times a week, (2) vigorous intensity level, (3) exercise for weight or shape reasons and (4) perceived ‘obligatory’ character. Therapy motivation will be examined using the therapy motivation questionnaire (Fragebogen zur Messung der Psychotherapiemotivation (FPTM-23)).^72^ We will further conduct semistructured trial completion interviews. This includes a ‘funnelled debriefing’ procedure (ie, asking increasingly specific questions about the trial hypothesis and different treatment arms) to evaluate patient blinding,^73^ and open-ended questions concerning reasons for trial dropout or premature cessation, if applicable.

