### Sample size

We employed a hypothesis testing approach for feasibility outcomes developed by Lewis *et al*^75^ to determine the sample size for the proposed feasibility trial. The rationale of this approach is that we determine a sample size that will allow us to test an observed feasibility outcome (eg, the adherence rate) against being in the defined red zone (unacceptable rate), based on an expectation of it being in the defined green zone (acceptable rate). In other words, we define a null hypothesis (the true feasibility outcome is not greater than the value demarcating the red zone) and an alternative hypothesis (the true feasibility outcome is greater than the value demarcating the red zone by magnitude of its difference towards the value demarcating the green zone). The study is then powered for a one-sided test to detect the difference between red and green zones. The amber zone (between red and green) is then split into two areas (major and minor amend) by the critical boundary of the corresponding test. For the proposed trial, α (one tailed) and β were set to.05.

The sample size calculations are listed in table 1 and were based on binomial exact tests (for tolerability and adherence rates) and a one-sample t-test (for acceptability means), respectively. The maximum sample size suggested by the Lewis approach is n=21 for evaluating adherence. We therefore targeted the recruitment of 42 patients to be randomly allocated to either the intervention arm or the control condition for an intention-to-treat analysis.

**Table 1 T1:** Sample size calculations

Feasibility outcome	Green zone	Red zone	Required n***
Acceptability (mean SUS across patients; SD=22.5^84^)	>70	<50	16
Tolerability (% of patients with SSQ mean≥40)	<60	>95	14
Adherence (% of patients with exposure mean≥12 min)	>84	<50	21

Note. Observed values in-between green and red zones provide no clear evidence for or against feasibility. This may signal to discuss steps to amend the trial procedures or re-evaluate progression criteria. *n designates the minimum number of recruited per study arm based on binomial exact tests (for Tolerability and Adherence rates) and a one-sample -test (for Acceptability means), respectively.

* n designates the minimum number of recruited patients per study arm based on binomial exact tests (for tolerability and adherence rates) and a one-sample t-test (for acceptability means), respectively.

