SSQSimulation Sickness QuestionnaireSUSSystem Usability Scale

For the analysis, the ‘traffic light’ approach will be applied. Each outcome is considered separately, and overall progression is then determined by the worst performing criterion (ie, go, if all outcomes are green; stop, if one outcome is red; amend, if one outcome is in the amber zone, but none are red). The probabilities for the wrong decision for the three feasibility outcomes with the planned sample size of 21 per arm is shown in table 2. Combined, the probability of falsely not progressing to the full trial is smaller than the sum of probabilities to falsely fall within the red zone and hence is smaller than 0.07%.

**Table 2 T2:** Probabilities for the wrong decision for the three feasibility outcomes

Probability if true value within	Red zone and falsely observed value within green zone	Green zone and falsely observed value within red zone
Acceptability	0.03%	0.03%
Tolerability	<0.01%	0.03%
Adherence	0.07%	0.01%

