### Assignment of interventions

Participants will be randomly assigned to either control or intervention conditions with a 1:1 allocation as per a specified randomisation schedule using permuted blocks of random sizes. Randomisation will be conducted by a staff member not involved in the recruitment or interviews. An independent researcher blinded to the patient’s intervention group will conduct all interviews and transfer the data into the database to avoid any detection bias. Blinding of the researcher administering the intervention was deemed infeasible, but patients will be blinded as per the different trial conditions, and we will encourage patients to not share their specific VR experiences with other therapists or patients. The researcher administering the intervention will otherwise not be involved in the patient’s overall treatment, such that performance biases are unlikely.

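### The weight-gain safety statement calls the intervention unsafe on any shortfall against control, with no margin or interval, and the progression rule does not use the result

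*Protocol article*

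**What the plan says.** Under Outcomes, the protocol article lists the rate of weight gain as a safety assessment and states that "the intervention would be unsafe, if successful weight gain rates in the intervention condition fall below the weight gain rates in the control condition". This is the only definition of unsafe in the document. Just before it comes the benchmark "Current treatment guidelines propose weight gains of 500 g per week", which is not named as the cut-off for a successful gain. The same section defines the secondary weight outcome as change in BMI.

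The progression rule under Sample size is "go, if all outcomes are green; stop, if one outcome is red", with amend in between. It is applied to the three feasibility outcomes in Tables 1 and 2: acceptability, tolerability and adherence. Trial design and Data analysis describe the same scope. Weight gain has no zone and appears in neither table.

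Data analysis gives weight gain an exploratory ANCOVA of the end-of-treatment value on group, baseline value and AN subtype. It describes no comparison of success rates. Data monitoring provides a DSMB that follows safety, but does not mention the weight criterion or connect the board's view to progression.

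**The concern.** There are two problems.

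- **The label is driven by chance.** If unsafe means that the observed intervention rate is lower than the observed control rate, one fewer success is enough. With about 20 patients per arm, the sign of such a difference carries little information when the true rates are equal or close.
- **The label leads nowhere.** No section says what happens if it applies. A trial with three green outcomes and an unsafe verdict on weight would be a go under the stated rule.

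Weight restoration is, in the protocol's own words, a main aim of treatment, so this is the natural place for a harm signal to appear. As written, the plan could attach a damaging label to a harmless add-on by chance. It could equally leave a real signal to be argued over after the data are seen.

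**Working it through.** **Inputs from the document.** Arm size is 21 ("with the planned sample size of 21 per arm"), from 42 patients randomised "with a 1:1 allocation as per a specified randomisation schedule using permuted blocks of random sizes". For the feasibility outcomes only, "α (one tailed) and β were set to.05". The adherence limits are 50% (red) and 84% (green).

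**Assumed input.** The common weight-gain success rate p is not given, so it is varied from 5% to 95%.

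**Step 1: reproduce the plan's own figure.** For adherence with n = 21, the exact one-sided test rejects 50% at 15 or more adherent patients. P(X ≥ 15 | p = 0.50) = 0.039 and P(X ≥ 15 | p = 0.84) = 0.961. The stated 21 per arm is reproduced. Tolerability (14) and acceptability (16) also reproduce, as do the Table 2 probabilities, the largest of which is 0.07%.

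**Step 2: no true effect on weight.** Let X_I and X_C be independent Bin(21, p). By symmetry, P(X_I < X_C) = (1 − P(tie))/2, where P(tie) is the sum over k of P(X = k)². At p = 0.5, P(tie) = 0.1224, so the result is (1 − 0.1224)/2 = 0.439.

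| Assumed common rate | P(tie) | P(labelled unsafe) |
|---|---|---|
| 5% or 95% | 0.302 | 34.9% |
| 10% or 90% | 0.209 | 39.6% |
| 20% or 80% | 0.154 | 42.3% |
| 30% or 70% | 0.134 | 43.3% |
| 40% or 60% | 0.125 | 43.8% |
| 50% | 0.122 | 43.9% |

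About 44% is therefore the maximum under the binary reading. If mean gains on a continuous scale are compared, ties vanish and the figure is 50%. With 17 patients per arm and p = 0.5 it is 43.2%, so dropout hardly matters.

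**Step 3: true differences.** P(X_I < X_C) is the sum over k of P(X_I = k)·P(X_C > k).

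- Deficit, 40% against 50%: labelled unsafe 69.2%, so missed 30.8%.
- Benefit, 60% against 50%: labelled unsafe 20.8%.

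**Step 4: precision.** The approximate 95% half-width for a difference in proportions at p = 0.5 is 1.96 × √(2 × 0.25/21) = 0.30, or 30 percentage points.

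**Step 5: what a strict interval rule would do.** Suppose unsafe required the upper limit of a Wald 90% interval to lie below zero. Enumerating all pairs of outcomes gives:

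| True rates (intervention, control) | Sign rule | Upper 90% limit < 0 |
|---|---|---|
| 50%, 50% | 43.9% | 4.8% |
| 40%, 50% | 69.2% | 16.0% |
| 30%, 50% | 88.3% | 39.2% |

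The strict rule removes most false labels but loses most of the sensitivity.

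**The case against.** The strongest reply is that the sentence is a rationale and not an operating rule. It does not say that point estimates are compared, when, or per patient or per week, and the hypotheses under Sample size are worded in true values. An analysis plan that is not shown may supply the method. This has force as regards the calculation: the percentages apply to one reading, and to success rates that the document does not give. It does not remove the problem, because the sentence is the only definition of unsafe, and its plain wording is met by any shortfall.

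A second reply is that safety is already handled by the DSMB and by the planned ANCOVA. The ANCOVA will indeed give an adjusted between-arm difference, so it would be wrong to say that the trial yields no usable information on weight. Neither provision is tied to the stated criterion or to progression, however.

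A third reply is that a sensitive alarm suits a small trial in underweight patients, and that keeping safety apart from a feasibility traffic light is a legitimate choice. Both points stand as design preferences. They argue against replacing the statement with a demand for demonstrated harm, as Step 5 shows. They do not justify a definitive label resting on a sign, or silence on what follows from it.

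A reader might infer that a harmless intervention would fail the trial about 44% of the time. The document does not support that. The label triggers no stop signal, and the 44% is the top of an assumption-based range.

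**Conclusion.** The point holds as a fault in a stated rule. Under the observed-rate reading with 21 per arm, an intervention with no effect on weight is labelled unsafe 42% to 44% of the time for common success rates of 20% to 80%, falling to 35% at 5% or 95%. It is 50% if means are compared. A true 10-point deficit from 50% is missed 31% of the time. These figures assume independent patients, one binary outcome each, and success rates that the document does not state.

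Separately, and with no assumption needed, the protocol permits a go decision for an intervention that meets its own definition of unsafe. The Outcomes, Trial design, Sample size and Data analysis sections must be reconciled.

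The fault should be fixed, but it does not undermine the trial's main purpose. The primary endpoints, the sample size and Table 2 are unaffected.

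**What to change.** 1. Reword the safety statement so that the sign of the observed difference alone does not define unsafe, and state what counts as a successful gain and in which unit.
2. Report the between-arm difference in success proportion and the baseline-adjusted difference in weight gain from the ANCOVA already planned, each with a confidence interval.
3. Treat any numerical shortfall as a signal for DSMB review.
4. State in the progression rule how the DSMB's conclusion on weight bears on go, amend and stop.
5. Leave any margin or criterion for declaring harm to the sponsor and DSMB, fixed in advance. They should know that requiring an upper 90% limit below zero would flag a true 10-point deficit (40% against 50%) only 16% of the time.

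The cost is a change of wording and one additional estimate from weights already recorded weekly. The shortfall signal will still fire often by chance, but it would then prompt a review instead of a verdict. The safety statement becomes less definite, which is all that 21 per arm can support.

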### Participant timeline

Because changes during the first 3–4 weeks are critical for overall AN treatment outcomes,^16^,^18^ the VR intervention or control procedure will be delivered on a weekly basis over the course of the initial four consecutive weeks of AN treatment. On admission, we will screen patient records based on diagnosis, age and BMI. Patients potentially meeting inclusion criteria will be assessed for eligibility and, if eligible and willing to participate, randomised to receive the VR intervention or VR control procedure on a weekly basis over the course of the four consecutive weeks. A weekly schedule with two sessions will be implemented as we expect daily experiences (eg, supervised meals, weighing and mirror exposure as part of regular inpatient treatment) to trigger activity urges repeatedly, thus requiring regular and repeated attendance. The proposed trial duration and frequency of visits are similar to other VR-based exposure therapies for patients with AN.^49 52 74^

At enrolment, we will record patient height and body weight, and diagnosis (based on ICD-10 criteria), and patients will be asked to complete a sociodemographic questionnaire, the EDE-Q, the CES, the FPTM-23 and a brief excessive PA interview. At the end of each week during the trial, patients will complete the SUPA-Q, the EDE-Q, and we will record patients’ current weight. After each session, patients will provide acceptability and tolerability ratings, and we will record the duration of completed exposure sessions. We will record the reasons, if sessions are terminated prematurely. At close-out, we will evaluate patient blinding in a close-out interview, and record patient weight, SUPA-Q and EDE-Q scores (see figure 2).

**Figure 2 F2:**
[figure not shown]
Participant timeline schematic diagram. CES, Commitment to Exercise Scale; EDE-Q, Eating Disorder Examination-Questionnaire; FPTM-23, Fragebogen zur Messung der Psychotherapiemotivation; SUPA-Q, State Urge to be Physically Active-Questionnaire; VR, virtual reality.

### Sample size

We employed a hypothesis testing approach for feasibility outcomes developed by Lewis *et al*^75^ to determine the sample size for the proposed feasibility trial. The rationale of this approach is that we determine a sample size that will allow us to test an observed feasibility outcome (eg, the adherence rate) against being in the defined red zone (unacceptable rate), based on an expectation of it being in the defined green zone (acceptable rate). In other words, we define a null hypothesis (the true feasibility outcome is not greater than the value demarcating the red zone) and an alternative hypothesis (the true feasibility outcome is greater than the value demarcating the red zone by magnitude of its difference towards the value demarcating the green zone). The study is then powered for a one-sided test to detect the difference between red and green zones. The amber zone (between red and green) is then split into two areas (major and minor amend) by the critical boundary of the corresponding test. For the proposed trial, α (one tailed) and β were set to.05.

The sample size calculations are listed in table 1 and were based on binomial exact tests (for tolerability and adherence rates) and a one-sample t-test (for acceptability means), respectively. The maximum sample size suggested by the Lewis approach is n=21 for evaluating adherence. We therefore targeted the recruitment of 42 patients to be randomly allocated to either the intervention arm or the control condition for an intention-to-treat analysis.

**Table 1 T1:** Sample size calculations

Feasibility outcome	Green zone	Red zone	Required n***
Acceptability (mean SUS across patients; SD=22.5^84^)	>70	<50	16
Tolerability (% of patients with SSQ mean≥40)	<60	>95	14
Adherence (% of patients with exposure mean≥12 min)	>84	<50	21

Note. Observed values in-between green and red zones provide no clear evidence for or against feasibility. This may signal to discuss steps to amend the trial procedures or re-evaluate progression criteria. *n designates the minimum number of recruited per study arm based on binomial exact tests (for Tolerability and Adherence rates) and a one-sample -test (for Acceptability means), respectively.

* n designates the minimum number of recruited patients per study arm based on binomial exact tests (for tolerability and adherence rates) and a one-sample t-test (for acceptability means), respectively.

SSQSimulation Sickness QuestionnaireSUSSystem Usability Scale

For the analysis, the ‘traffic light’ approach will be applied. Each outcome is considered separately, and overall progression is then determined by the worst performing criterion (ie, go, if all outcomes are green; stop, if one outcome is red; amend, if one outcome is in the amber zone, but none are red). The probabilities for the wrong decision for the three feasibility outcomes with the planned sample size of 21 per arm is shown in table 2. Combined, the probability of falsely not progressing to the full trial is smaller than the sum of probabilities to falsely fall within the red zone and hence is smaller than 0.07%.

**Table 2 T2:** Probabilities for the wrong decision for the three feasibility outcomes

Probability if true value within	Red zone and falsely observed value within green zone	Green zone and falsely observed value within red zone
Acceptability	0.03%	0.03%
Tolerability	<0.01%	0.03%
Adherence	0.07%	0.01%

### Recruitment

We will screen patients and assess patients for eligibility until achieving the target sample size. Admission statistics of the study centre reveal that an average of 362 patients present with an eating disorder (ED) throughout a year, with 196 patients treated in 2022 meeting the key inclusion criteria for the trial (adult, AN diagnosis, BMI<17.5 kg/m²). Based on these numbers and the analysis goal, we targeted the recruitment of 42 patients in a 16-month window. This corresponds to a recruitment rate of approximately 22% (the equivalent of two to three patients per month).

### Assignment of interventions

Participants will be randomly assigned to either control or intervention conditions with a 1:1 allocation as per a specified randomisation schedule using permuted blocks of random sizes. Randomisation will be conducted by a staff member not involved in the recruitment or interviews. An independent researcher blinded to the patient’s intervention group will conduct all interviews and transfer the data into the database to avoid any detection bias. Blinding of the researcher administering the intervention was deemed infeasible, but patients will be blinded as per the different trial conditions, and we will encourage patients to not share their specific VR experiences with other therapists or patients. The researcher administering the intervention will otherwise not be involved in the patient’s overall treatment, such that performance biases are unlikely.

### Data collection methods

All quantitative data will be collected pseudonymously via electronic data capture tools (see below). ICD-10-based diagnosis, height and medications will be obtained from patient records. Patients will self‐report their age, sex, sexual orientation, German language ability, migration background, years of education, marital status, living circumstances, days in current treatment and previous treatments. Acceptability will be measured with the SUS.^64^ The SUS is a widely used instrument that measures the subjective usability of products and systems with 10 questions on a 5-point scale (from *strongly disagree* to *strongly agree*), which, after linear transformations, are scored on a range from 0 (low usability) to 100 (high usability). The German SUS^76^ has good reliability (Cronbach’s α=0.84). Tolerability will be measured using the SSQ.^64 65^ The SSQ asks patients to rate 16 symptoms on a scale from 0 to 3 (none, slight, moderate and severe), with a weighted sum score (Cronbach’s α=0.84) indicating overall severity.^77^ Intervention adherence is measured in minutes of completed VR exposure using a stop watch.

Patient weight will be assessed using a calibrated scale (KERN & SOHN GmbH, Balingen-Frommern, Germany). Activity urges will be recorded using the validated state activity urges questionnaire (SUPA-Q).^55^ Its 21 items assess current activity urges (eg, ‘I have the urge to be physically active right now’) on a 5-point scale from 1 (not at all, 0%) to 5 (a great deal, 100%) and can be aggregated into a total score reflecting a single latent factor (Cronbach’s α=0.95). Eating disorder psychopathology is assessed with the EDE-Q.^70^ The EDE-Q contains 22 attitudinal items that can be combined into a global score of cognitive and behavioural ED symptoms over the last 28 days (Cronbach’s α=0.94) rated on a 7-point scale (from 0, never, to 6, every day). We will use a version with a slightly modified instruction to assess ED symptoms within the past week. The CES,^71^ with eight items rated on a visual analogue scale (horizontal line of 12.2 cm) with bipolar adjectives on each end, will be used to assess obsessive–compulsive aspects of PA (Cronbach’s α=0.82). Excessive PA status in the 28 days prior to admission will be assessed during a face-to-face interview and categorised using the criteria: (1) ≥1 hour a day and/or ≥5 times a week, (2) vigorous intensity level, (3) exercise for weight or shape reasons and (4) perceived ‘obligatory’ character. Therapy motivation will be examined using the therapy motivation questionnaire (FPTM-23).^72^ The FPTM-23 includes 23 items rated on a 4-point scale (agree, somewhat agree, somewhat disagree, disagree), which are summed into various subscales (Cronbach’s α≥0.78).

